## Dose Escalation Schema

Dose escalation will proceed within each cohort according to the following schema (Table 9).

**Table 9:** Dose escalation schema for each cohort as defined by hepatic function.

|            | Group A                 | Group B                  | Group C                      | Group D                    |
|------------|-------------------------|--------------------------|------------------------------|----------------------------|
|            | Normal hepatic function | Mild hepatic dysfunction | Moderate hepatic dysfunction | Severe hepatic dysfunction |
| Dose Level | mg                      | mg                       | mg                           | mg                         |
| Level - 2  | -                       | 1                        | 0.5                          | -                          |
| Level - 1  | -                       | 1.5                      | 1                            | 0.5                        |
| Level 1    | 2                       | 2                        | 1.5                          | 1                          |
| Level +1   | no escalation           | no escalation            | 2                            | 1.5                        |
| Level +2   | no escalation           | no escalation            | no escalation                | 2                          |

Dose-limiting toxicity (DLT) is defined above (Sections 5.3.1. and 5.3.2).

The patient's starting dose will be assigned by the Central Office Study Coordinator at the time of registration. The patients' hepatic dysfunction group may be altered after registration if hepatic function tests performed within 24 hours of commencing trametinib have changed from registration results as described in section 5.1.1. The dose may be reduced for individual patients in subsequent cycles depending on toxicity as outlined in section 6.

Normal, mild, moderate and severe liver dysfunction cohorts may be open concurrently.

The initial cohorts of patients will begin on dose level 1 based on their level of hepatic dysfunction. Liver function tests (AST and total bilirubin) should be repeated within 24 hours prior to starting treatment on study to determine hepatic dysfunction cohort.

Escalation is planned as the standard "3+3" schema, for each hepatic dysfunction cohort (Cohorts B, C and D), with the exception of the normal hepatic function cohort (Cohort A) (Table 10).

**Table 10:** Dose escalation and cohort expansion rules using the standard 3+3 design.

| Number of Patients with DLT at a Given Dose Level                         | Escalation Decision Rule                                                                                                                                                                                                                                                                                                                                                                                                                                        |
|---------------------------------------------------------------------------|-----------------------------------------------------------------------------------------------------------------------------------------------------------------------------------------------------------------------------------------------------------------------------------------------------------------------------------------------------------------------------------------------------------------------------------------------------------------|
| 0 out of 3                                                                | Enter 3 patients at the next dose level.                                                                                                                                                                                                                                                                                                                                                                                                                        |
| ≥ 2                                                                       | Dose escalation will be stopped. This dose level will be declared the maximally administrated dose (highest dose administrated). Three (3) additional patients will be entered at the next lowest dose level if only 3 patients were treated previously at that dose.                                                                                                                                                                                           |
| 1 out of 3                                                                | Enter at least 3 more patients at this dose level. 
 
If 0 of these 3 patients experience DLT, proceed to the next dose level.
 
If 1 or more of this group suffer DLT, then dose escalation is stopped, and this dose is declared the maximally administrated dose. Three (3) additional patients will be entered at the next lowest dose level if only 3 patients were treated previously at that dose.
 
 |
| ≤ 1 out of 6 at highest dose level below the maximally administrated dose | This is generally the recommended phase 2 dose. At least 6 patients must be entered at the recommended phase 2 dose.                                                                                                                                                                                                                                                                                                                                            |

No more than 12 patients will be enrolled to the normal hepatic function cohort, which serves as a pharmacokinetic comparison. For safety reasons, patients in the severe dysfunction cohort will be enrolled one patient at a time (i.e., the second patient in the severe cohort will not be enrolled until the first patient completes cycle 1 and so on for each subsequent patient). This one by one rule applies only while the same dose level for the moderate hepatic dysfunction group is incomplete (i.e. if moderate cohort at 1.5 mg/day of trametinib is not completed, severe cohort can be opened at the same dose level but no more than 1 patient can be enrolled until the same dose level in the moderate cohort has been cleared); once complete, we can enroll to the severe cohort as usual (see also Section 13.2). Patients with normal and mild hepatic function will not have their dose escalated.

Doses in more severe cohorts will not be escalated beyond doses being tested in less severe cohorts. If DLT-level toxicity is noted in dose level 1, then dose de-escalation to level -1 may occur (except for the normal hepatic function cohort). A patient may be dose reduced to the next lowest dose level if they experience and recover from a Grade 4 adverse event as outline in Section 6, but this should be discussed first with the Principal Investigator.

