### 13.3 Stratification Factors

Patients will be stratified according to level of hepatic dysfunction as summarized in the table below (Table 27) and described in Section 5.1. Dose escalation and determination of the MTD will be carried out separately for each cohort or stratum. For Cohort A, no MTD or RP2D will need to be defined as this group has normal liver function. For Cohorts B, C and D, the 3+3 rule will be used to define the RP2D, such that for each Cohort, the highest level in which  $\leq 1$  out of 6 patients experienced DLT, at or below the maximum administered dose, would constitute the RP2D. If  $\leq 1$  of 6 patients experienced DLTs at the maximum administered dose, then the maximum administered dose will be declared RP2D for that cohort.

**Table 27:** Defining criteria for the four cohorts based on hepatic function.

| Group | Hepatic Function             | Hepatic Function                                                                               |
|-------|------------------------------|------------------------------------------------------------------------------------------------|
| A     | Normal hepatic function      | Bilirubin $\leq$ ULN
AST $\leq$ ULN                                                         |
| B     | Mild hepatic dysfunction     | B1: bilirubin $\leq$ ULN and AST $>$ ULN
B2: ULN $<$ bilirubin $\leq 1.5$ x ULN and any AST |
| C     | Moderate hepatic dysfunction | 1.5x ULN $<$ bilirubin $\leq 3$ x ULN and any AST                                              |
| D     | Severe hepatic dysfunction   | 3x ULN $<$ bilirubin $\leq 10$ x ULN and any AST                                               |

Further exploratory analysis may be performed using the clinical and pharmacokinetic data collected from this study based on patients' Childs-Pugh Classification.

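### The sentence allowing de-escalation from dose level 1 gives no DLT count and does not agree with Table 10, yet it is the only text that opens level −1

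*Protocol*

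**What the plan says.** Groups B, C and D start at level 1 (2, 1.5 and 1 mg in Table 9) and follow a 3+3 scheme set out in Table 10 of the Dose Escalation Schema:

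- 0 of 3 with DLT: "Enter 3 patients at the next dose level".
- 1 of 3: "Enter at least 3 more patients at this dose level". Then, "If 0 of these 3 patients experience DLT, proceed to the next dose level". If one or more of the added patients has a DLT, escalation stops.
- Two or more: escalation stops and the level becomes the maximally administered dose. "Three (3) additional patients will be entered at the next lowest dose level if only 3 patients were treated previously at that dose". The stopping branch of the 1-of-3 row carries the same condition.
- Recommended dose: "≤ 1 out of 6 at highest dose level below the maximally administrated dose", with a minimum of six patients at that dose.

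The paragraph after the table adds, outside any count: "If DLT-level toxicity is noted in dose level 1, then dose de-escalation to level -1 may occur", except in the normal-function cohort.

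Section 13.3 states that the 3+3 rule defines the recommended dose in B, C and D as the highest level with at most 1 DLT in 6, "at or below the maximum administered dose, would constitute the RP2D". Section 13.2 gives Group B a minimum of 3 patients and the trial a minimum of 27. Table 9 lists a level −2 for Groups B and C.

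**The concern.** Dosing recommendations and the MTD by hepatic group are primary objectives (Section 1.1), so the rule for leaving a level should be fixed. With one DLT in the first three patients at level 1, Table 10 requires expansion of that level, while the sentence after it permits the cohort to leave. Two teams with the same data could both follow the protocol and end at different doses.

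The question is sharpest in structure for Group B. Its level 1 is both starting dose and ceiling, so all dose finding there is downward, and Table 10 is written mainly for going up. The related statements on the maximum administered dose and on Group B's minimum accrual add to the uncertainty about what completes a cohort.

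**Working it through.** **Stated accrual.** Section 13.2: minimum 12 + 3 + 6 + 6 = 27; maximum 12 + 12 + 22 + 22 = 68. Both totals reproduce. The protocol states no DLT rate, so p below is assumed.

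**Is the sentence needed?** When Table 10 stops level 1, it enters patients one level down only if three were treated there before. All cohorts begin at level 1, so level −1 has had none and the condition is not met. The sentence is therefore the only text that sends a cohort to level −1. It names no other level. Table 10's condition fails in the same way for level −2, so no text states when a cohort would move there.

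**Where the two lines part.** Let P0 = (1−p)³ and P1 = 3p(1−p)² be the chances of 0 and 1 DLT in three patients at level 1.

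- Level 1 left on any DLT in the first three: 1 − P0.
- Level 1 stopped under Table 10: (1 − P0 − P1) + P1(1 − P0).
- Difference: P1 × P0 = 3p(1−p)⁵, the path 1/3 then 0/3.

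| Assumed p | P1 | Any DLT | Table 10 | Difference |
|---|---|---|---|---|
| 0.10 | 24.3% | 27.1% | 9.4% | 17.7% |
| 0.15 | 32.5% | 38.6% | 18.6% | 20.0% |
| 0.20 | 38.4% | 48.8% | 29.1% | 19.7% |
| 0.30 | 44.1% | 65.7% | 50.6% | 15.1% |

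For p = 0.20: P0 = 0.8³ = 0.512, P1 = 3 × 0.2 × 0.64 = 0.384, and P1 × P0 = 0.197.

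**Effect on the recommended dose in Group B.** With six patients at 2 mg, Table 10 and Section 13.3 retain that level with probability (1−p)⁶ + 6p(1−p)⁵. If any DLT in the first three leads to level −1, it is retained with probability P0(P0 + P1).

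- p = 0.10: 88.6% against 0.729 × 0.972 = 70.9%
- p = 0.20: 65.5% against 0.512 × 0.896 = 45.9%
- p = 0.30: 42.0% against 0.343 × 0.784 = 26.9%

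The gaps equal the differences in the table.

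**Group B's minimum.** Six patients are required at the recommended dose, so Group B cannot yield one with 3 patients. With 6 in place of 3, the total minimum is 12 + 6 + 6 + 6 = 30.

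**The case against.** The strongest reply is that this is loose drafting, not two opposed rules. The sentence says de-escalation may happen; it does not say that one DLT is enough. The 3+3 scheme is named as governing in the Dose Escalation Schema and in Section 13.3, and Section 12.1 requires Principal Investigator sign-off for every escalation, expansion or de-escalation. On that view the sentence means only that level −1 is available once Table 10 has stopped level 1. The reading is reasonable, and it makes the figures above an upper bound. But no text ties the sentence to a count, and sign-off leaves the choice at 1/3 to discretion.

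Four stronger readings are tempting, and the documents do not support them:

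- A reader might infer that nobody can be enrolled at level −1 after two or more DLTs. The sentence fills that gap, though without a count.
- A reader might infer that 0/3 at level −1 sends patients back up to the level just stopped. Table 10 says escalation has ended by then, and the six-patient requirement points to completing level −1.
- A reader might infer that the two recommended-dose statements yield different doses. In Table 10 the maximally administered dose has met a stopping count, so it cannot also have at most 1 DLT in 6. For a tolerated top level, Section 13.3 gives the answer expressly. This is one term used in two senses.
- A reader might infer that Group B is numerically worst affected. At equal p the 1/3-then-0/3 path is equally likely in C and D.

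**Conclusion.** The point holds as an unresolved rule on a primary objective. At 1 DLT in 3 at level 1, Table 10 requires expansion and the following sentence permits departure. That sentence cannot be ignored, because it is the only way to level −1, and cohort use of level −2 has no rule at all. The two uses of the maximum administered dose, and Group B's minimum of 3 against the required 6, need settling at the same time.

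The possible difference in recommended dose arises on the path 1/3 then 0/3, about 15–20% for DLT rates of 10–30%. Those rates are assumed, and the figure is reached only if the option to de-escalate is always taken at 1/3. The documents do not show that a single DLT forces a cohort off level 1.

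**What to change.** The sponsor should reconcile the sentence after Table 10, Table 10 itself and Section 13.3, so that:

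1. one stated DLT count governs leaving level 1;
2. the condition for entering a lower level covers a level with no prior patients, and states whether and when level −2 is used as a cohort dose;
3. the maximum administered dose has one definition in Table 10 and Section 13.3.

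Section 13.2 should restate Group B's minimum to agree with the six-patient requirement. If it becomes 6, the total minimum moves from 27 to 30. Which rule governs is for the sponsor to decide.

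The cost is protocol wording, a matching change to the IWRS cohort rule and a slightly higher stated minimum accrual.

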#### **5.4 General Concomitant Medication and Supportive Care Guidelines**

Because there is a low potential for interaction of trametinib with other concomitantly administered drugs through the cytochrome P450 system, the case report form must capture the concurrent use of all other drugs, over-the-counter medications, or alternative therapies. The Principal Investigator should be alerted if the patient is taking any agent known to affect or with the potential to affect selected CYP450 isoenzymes.

#### **5.5 Duration of Therapy**

In the absence of treatment delays due to adverse event(s), treatment may continue until one of the following criteria applies:

- Disease progression,
- Intercurrent illness that prevents further administration of treatment,
- Unacceptable adverse event(s),
- Patient decides to withdraw from the study, or
- General or specific changes in the patient's condition render the patient unacceptable for further treatment in the judgment of the investigator.

#### **5.6 Duration of Follow Up**

Patients will be followed for 4 weeks after removal from study or until death, whichever occurs first. Patients removed from study for unacceptable adverse event(s) will be followed until resolution or stabilization of the adverse event.

#### **5.7 Criteria for Removal from Study**

Patients will be removed from study when any of the criteria listed in Section 5.5 applies. The reason for study removal and the date the patient was removed must be documented in the Case Report Form.

## 6. DOSING DELAYS/DOSE MODIFICATIONS

The start (day 1) of subsequent cycles after cycle 1 can be delayed by up to three to four weeks (based on the adverse event causing the delay, as specified in this Section), but missed doses due to delays are not made up.

Dose reductions for toxicities not meeting DLT criteria may be considered for individual patients but only after consultation with the Principal Investigator. There is a maximum of 2 dose reductions per patient, after which they will be removed from the study. Dose reductions below 0.5 mg QD are not allowed.

### 6.1 Trametinib Dimethyl Sulfoxide (GSK1120212B, MEKINIST™) Dose Modifications

The table (Table 11) below outlines the dose levels to be used for any necessary trametinib dose modifications:

**Table 11:** Dose modification schema for each cohort as defined by hepatic function.

|                   | Group A                     | Group B                      | Group C                          | Group D                        |
|-------------------|------------------------------------|-------------------------------------|-----------------------------------------|---------------------------------------|
|                   | Normal
hepatic function | Mild
hepatic dysfunction | Moderate
hepatic dysfunction | Severe
hepatic dysfunction |
| Dose Level | mg                                 | mg                                  | mg                                      | mg                                    |
| Level - 2         | 1*                                 | 1                                   | 0.5                                     | -                                     |
| Level - 1         | 1.5*                               | 1.5                                 | 1                                       | 0.5                                   |
| Level 1           | 2                                  | 2                                   | 1.5                                     | 1                                     |
| Level +1          | no escalation                      | no escalation                       | 2                                       | 1.5                                   |
| Level +2          | no escalation                      | no escalation                       | no escalation                           | 2                                     |

\*To be used for dose modifications only

A maximum of two trametinib dose level reductions are allowed. If a third dose level reduction is required, treatment will be permanently discontinued.

If a dose reduction of trametinib is required, but the toxicity resolves and no additional toxicities are seen after two cycles of treatment, the dose of trametinib may be re-escalated but should not exceed 2 mg once a day.

Dose modification and AE guidelines are outlined in the sections below for AEs that are deemed possibly related to trametinib:

- AEs not otherwise specified
- Rash
- Visual changes
- Diarrhea
- Liver chemistry elevation
- Ejection fraction changes

- Hypertension
- Prolonged QTc
- Pneumonitis

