| 
1. Rash prophylaxis is recommended for the first 6 weeks of study treatment.
 
2. Moderate-strength topical steroids: Hydrocortisone 2.5% cream or fluticasone propionate 0.5% cream.
 
3. Approval of CTEP Medical Monitor is required to restart study treatment after >4 weeks of interruption.
 
4. Trametinib may be escalated to previous dose level if no rash is evident 4 weeks after restarting study treatment.
 |                                                                                                                                                                                                                            |                                                                                                                                                                                                                                                                                                                                                                                 |

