| 
1. Uncomplicated diarrhea defined by the absence of symptoms such as cramping, nausea/vomiting, <math>\geq</math> grade 2, decreased performance status, pyrexia, sepsis, neutropenia <math>\geq</math> grade 3, frank bleeding, and/or dehydration requiring intravenous fluid substitution.
 
2. Complicated diarrhea defined by the presence of symptoms such as cramping, nausea/vomiting, <math>\geq</math> grade 2, decreased performance status, pyrexia, sepsis, neutropenia <math>\geq</math> grade 3, frank bleeding, and/or dehydration requiring intravenous fluid substitution.
 
3. Loperamide should be made available prior to start of study treatment so loperamide administration can begin at the first signs of diarrhea.
 
4. Escalation of trametinib to previous dose level is allowed after consultation with the medical monitor and in the absence of another episode of complicated or severe diarrhea in the 4 weeks subsequent to dose reduction.
 |                                                                                                                                                                                                                                                                                                                                                                                                                                                                                                                                                                                                                                                                                                                                                 |                                                                                                                                                                                                                                                                                                                                                                                                                     |

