| Grade 2                                    | 
 
• CT scan (high-resolution with lung windows) recommended.
 
• Work-up for infection
 
• Consult pulmonologist
 
• Pulmonary function tests – if < normal, repeat every 8 weeks until <math>\geq</math> normal
 
• Bronchoscopy with biopsy and/or BAL recommended
 
• Symptomatic therapy including corticosteroids if clinically indicated
 
 | 
 
• Interrupt trametinib until recovery to grade <math>\leq 1</math>
 
• Restart treatment with trametinib reduced by one dose level
 
• Escalation to previous dose level after 4 weeks may be considered after consultation with medical monitor
 
• If no recovery to grade <math>\leq 1</math> within 4 weeks, permanently discontinue trametinib
 
 |
| Grade 3                                    | 
 
• Same as grade 2
 
                                                                                                                                                                                                                                                                                                                                                                  | 
 
• Interrupt trametinib until recovery to grade <math>\leq 1</math>
 
• After consultation with medical monitor, trametinib may be restarted reduced by one dose level
 
• If no recovery to grade <math>\leq 1</math> within 4 weeks, permanently discontinue trametinib
 
                                                                                   |

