## **13. STATISTICAL CONSIDERATIONS**

### **13.1 Study Design/Endpoints**

This phase 1 trial will use a design involving four cohorts of patients with different degrees of liver dysfunction.

- The dose escalation rules used in this study are adapted from the standard up-and-down "3+3" design, and maintain the basic principles of that design. Normal, mild, moderate and severe liver dysfunction cohorts may be open concurrently. The design has been modified for this organ dysfunction study to eliminate waiting periods between dose levels as the clinical stability of patients with impaired hepatic function is frequently limited, and it is thus unreasonable to delay therapy for 2-3 weeks in this patient population. The disadvantage of this approach is that it may increase the number of patients who receive a dose that is subsequently found to be above the recommended dose level. However, the benefit is expected to outweigh this risk as this population of patients is small, has few or no standard therapeutic options, and these patients usually have a limited timeframe during which therapy can be safely administered.
- Although dose-finding will be carried out independently for each of the liver dysfunction groups, an ancillary constraint is imposed: accrual to Group D (severe) will occur one patient at a time (i.e., the second patient in a cohort will not be enrolled until the first patient completes cycle 1 and so on for each subsequent patient until the equivalent moderate dose is complete), and the dose recommended for a group with greater liver dysfunction cannot be greater than that for a group with a lesser dysfunction. While it is conceivable that patients with greater liver dysfunction might tolerate the study drug better than those with lesser dysfunction, it is considered very unlikely. Furthermore, the highest dose to be explored is no greater than the recommended dose for patients with normal liver function. Thus, the ancillary constraint can do no harm; it is intended to compensate in part for patient heterogeneity and yield more accurate final recommended doses than possible with independent dose escalation in the four liver dysfunction groups.

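### Section 6.1 limits re-escalation only by a common 2 mg ceiling, which lies above the assigned dose in Groups C and D (and in Group B if de-escalated) and does not match the protocol's other dose limits

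*Protocol*

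**What the plan says.** Section 6.1 introduces Table 11 as the table that "outlines the dose levels to be used for any necessary trametinib dose modifications". Its Level 1 entries are 2 mg for Groups A and B, 1.5 mg for Group C and 1 mg for Group D. It lists 2 mg as Level +1 in Group C and Level +2 in Group D. No group has a level above 2 mg.

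Below the table, Section 6.1 allows a reduced dose to go back up once the toxicity has resolved and two further cycles have shown no additional toxicity: "the dose of trametinib may be re-escalated but should not exceed 2 mg once a day". No group, assigned dose or previous level is mentioned.

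Five event-specific rules say something narrower. For rash (Section 6.1.2): "Trametinib may be escalated to previous dose level if no rash is evident 4 weeks after restarting study treatment". For diarrhea (Section 6.1.4): "Escalation of trametinib to previous dose level is allowed after consultation with the medical monitor". For grade 2 pneumonitis (Section 6.1.6): "Escalation to previous dose level after 4 weeks may be considered after consultation with medical monitor". The footnotes for LVEF decrease (Table 17) and hypertension (Table 19) likewise refer to the previous level.

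Two cross-group limits stand elsewhere. The Dose Escalation Schema in Section 5.3 says "Doses in more severe cohorts will not be escalated beyond doses being tested in less severe cohorts". Section 13.1 says "the dose recommended for a group with greater liver dysfunction cannot be greater than that for a group with a lesser dysfunction".

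**The concern.** In an organ-dysfunction trial the dose ceiling should mean something different in each group. Section 2.4 anticipates higher trametinib concentrations in hepatic impairment, which is why Groups C and D start lower: "The initial cohorts of patients will begin on dose level 1 based on their level of hepatic dysfunction". For these groups 2 mg is a level to be reached through the 3+3 rules of Table 10. A single 2 mg ceiling on individual re-escalation takes no account of that.

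Read literally, the sentence lets a Group C or D patient who has already needed a reduction for toxicity go to a dose that has not been cleared in that group. The first stake is that patient's safety. The second is the toxicity tabulation by liver dysfunction group (Section 13.1), where later-cycle events could have occurred at doses not cleared for the group.

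**Working it through.** The protocol states no figure to reproduce here. The check compares the ceiling with the dose table and then sets the rules side by side.

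**Ceiling against own dose (Table 11), ratio = 2 mg / dose**

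| Group | Assigned dose | Ceiling / assigned | One level down | Ceiling / reduced |
|---|---|---|---|---|
| B, Level 1 | 2 mg | 2/2 = 1 | 1.5 mg | 2/1.5 = 1.33 |
| B, Level -1 | 1.5 mg | 2/1.5 = 1.33 | 1 mg | 2/1 = 2 |
| C, Level 1 | 1.5 mg | 2/1.5 = 1.33 | 1 mg | 2/1 = 2 |
| D, Level 1 | 1 mg | 2/1 = 2 | 0.5 mg | 2/0.5 = 4 |

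The excess over the assigned starting dose is 2 - 1.5 = 0.5 mg in Group C and 2 - 1 = 1 mg in Group D.

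**Does the ceiling do any work if re-escalation only means going back?** The highest level in every group is at most 2 mg, so a return to an earlier dose can never exceed 2 mg. On that reading the ceiling never binds. It has an effect only if a patient may go above the earlier dose.

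**Ceiling against the next less severe group.** At the starting levels it is 2 - 2 = 0 mg above Group B's dose for a Group C patient, and 2 - 1.5 = 0.5 mg above Group C's dose for a Group D patient.

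More generally, take B from {1, 1.5, 2}, C and D from {0.5, 1, 1.5, 2}, and keep D ≤ C ≤ B. With B at 1, 1.5 and 2 mg there are 3, 6 and 10 combinations, 19 in all.

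| Ceiling exceeds | Group C patient | Group D patient |
|---|---|---|
| own assigned dose | 15 of 19 | 18 of 19 |
| next less severe group's dose | 9 of 19 (all with B below 2 mg) | 15 of 19 |
| the same, with B at 2 mg | 0 of 10 | 6 of 10 |

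These counts describe the table; they are not probabilities.

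**Which reductions rely on the general sentence alone**

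- Table 12 (toxicities without their own section): reduces the dose and gives no rule for going back up.
- Grade 3 pneumonitis (Table 16): restart one level lower is possible; no upward rule.
- Grade 4 visual events with RPED and RVO excluded (Table 14): restart at the same or a reduced dose after discussion with the Medical Monitor; no upward rule.
- Grade 2-3 RPED: reduction by 0.5 mg, but patients on 1 mg discontinue. A Group D patient at the starting dose never reaches re-escalation here.
- Liver chemistry (Section 6.1.5): one level lower after recovery. The section has an upward rule tied to improved liver function, but none expressly for re-escalation after a toxicity reduction.

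**Timing.** DLTs count in cycle 1 only (Section 5.3). Mandatory PK is on days 15 and 16 of cycle 1 (Sections 9.1 and 9.1.2). Re-escalation under the general sentence comes after two further cycles, so it can affect neither.

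**The case against.** The strongest reply is that re-escalation after a reduction ordinarily means returning to the earlier dose, that a ceiling is not a target, and that five event rules use exactly that limit. This has force: the sentence is ambiguous and does not clearly authorise a dose above the assigned one. Moving a Group D patient from 0.5 to 2 mg would mean climbing three levels, and no passage describes such a step. But the reply leaves the 2 mg ceiling with nothing to do, and a site applying Table 12 has no other text to turn to.

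A reader might infer that the sentence breaches the cross-group dose limit. The documents do not support that. The limit in the Dose Escalation Schema is written for cohorts and the one in Section 13.1 for recommended doses; neither addresses one patient's later-cycle dose, and Section 6.1 does not claim to override them. For Group C nothing is exceeded while Group B is at 2 mg. For Group D there is an excess over Group C's dose only while Group C is below 2 mg, and it conflicts with the schema limit only if that limit is applied to individuals and against every less severe group. What stands is a mismatch with the intent of those limits.

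A reader might also infer damage to the dose-finding result. The timing rules that out for cycle 1 DLT counts, the MTD and mandatory PK. Only the later-cycle toxicity tabulation and optional repeat PK remain exposed.

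**Conclusion.** The point holds as a misaligned dose-modification rule. Section 6.1 sets one ceiling for all groups. At the starting levels it is 0.5 mg above the assigned dose in Group C and 1 mg above it in Group D, and it is above the assigned dose of any Group B patient assigned 1.5 or 1 mg. It differs from the five event-specific rules and is the only limit on going back up after Table 12 reductions and in the limited further cases listed.

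The ratios of up to 2 times the assigned starting dose and 4 times the reduced dose are literal upper bounds, not expected practice. They assume that the sentence is applied as written, without importing the limit used in the event tables. The consequence is for patient safety and for later-cycle toxicity by group. It does not reach the primary dose-finding conclusions, but the correction is easy and should be made.

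**What to change.** Reconcile the re-escalation sentence in Section 6.1 with the group-specific levels of Table 11, the event-specific rules in Sections 6.1.2, 6.1.4, 6.1.6, 6.1.7 and 6.1.9, and the cross-group limits in the Dose Escalation Schema and Section 13.1, so that a site finds one consistent limit for each group whatever toxicity caused the reduction. The text should also say whether the cross-group limits apply to individual patients after cycle 1. The waiting time and approval need the same reconciliation: the general sentence uses two cycles and mentions no approval, whereas the five event rules use 4 weeks and most require medical monitor consultation or approval.

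Which limit is right is a clinical decision for the sponsor and investigators; none is proposed here. The cost is about one sentence in Section 6.1, with no extra patients, procedures or analyses.
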